## Abstract

**Objective:**

Sleep disturbances are common non-motor symptoms of Parkinson's disease. The symptoms affect the quality of patients' life by impeding normal sleep cycles and causing excessive daytime sleepiness. Remote Ischemic Conditioning (RIC) is a therapy often used for ischemic stroke patients to minimize infarct size and maximize post-stroke neurological function. Animal experiments have shown that RIC plays a protective role for retinal ganglion cells and other critical areas of the brain of Parkinson's disease. However, whether RIC improves excessive daytime sleepiness (EDS) for patients with Parkinson's disease remains to be determined.

**Methods:**

This is a single-center, double-blind, and randomized controlled trial, which includes patients with Parkinson's disease with EDS. All recruited patients will be randomly assigned either to the RIC or the control group (i.e., sham-RIC) with 20 patients in each group. Both groups receive RIC or sham-RIC treatment once a day for 28 days within 24 h of enrollment. Epworth Sleepiness Scale (ESS), Pittsburgh Sleep Quality Index (PSQI), Parkinson Disease Sleep Scale-2 (PDSS-2), Parkinson's Disease Questionnaire39 (PDQ39) score scales, and adverse events, such as inability to tolerate the treatment leading to suspension of the study or objective signs of tissue or neurovascular injury caused by RIC and/or sham-RIC are evaluated at 7, 14, 28, and 90 days after enrollment.

**Results:**

The primary goal of this study is to assess the feasibility of the treatments in patients with Parkinson's disease by measuring serious RIC-related adverse events and any reduced incidence of adverse events during the trial and to study potential efficacy, improvement of patients' excessive daytime sleepiness, quality of life-based on ESS, PSQI, PDSS-2, and PDQ39 scores. The secondary goal is to confirm the safety of the treatments.

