### Interventions

Within 24 h of enrollment, an RIC operation is to be performed *via* bilateral limb ischemic preconditioning (Doctormate, IPC-906D, produced by Beijing Renqiao Institute of Neuroscience). Electronic tourniquet cuffs are placed on both arms. Participants in the intervention group undergo five cycles of cuff inflation to 200 mmHg for 5 min, followed by deflation for 5 min (Figure 1). In other studies, physical treatments, such as bright light therapy (35) and multidisciplinary intensive rehabilitation (36), have been applied to patients for 28 days to alleviate sleep disorders of Parkinson's disease. Additionally, RIC has been used for patients from 7 to 300 days (37–43). As the first step to determine safety, the duration of RIC in this study is decided to be 28 days. Patients in the sham-RIC group receive the same procedure except the maximum inflation pressure is 60 mmHg (40) (Figure 2).

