### Outcomes

#### Outcomes for feasibility and efficacy

The primary outcomes of this study are to assess the feasibility and efficacy of RIC from changes of ESS, PSQI, PDSS-2, and PDQ39 scores from the baselines to post-treatment on days 7, 14, 28, or 90. This study will determine (1) whether ESS, PSQI, PDSS-2, and PDQ39 can be performed in the patients and (2) the differences between ESS, PSQI, PDSS-2, and PDQ39 in patients with or without RIC. Certified therapists and assistants will collect data from the subjects and the obtained information will be used for statistical analysis.

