#### Outcomes for safety

The secondary outcome of this study is to assess the safety of RIC. Any serious RIC-related adverse events are the following: (1) inability to tolerate RIC or sham-RIC procedures leading to the suspension of the study; (2) signs of tissue or neurovascular injury caused by RIC and sham RIC operations (e.g., palpation of distal radial artery pulsation, visual inspection of local edema, erythema and skin damage, or palpation of tenderness). All adverse events will be independently determined by trained individuals of the research group who are blinded by random grouping.

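### The abstract ties the primary feasibility goal to an undefined reduction in adverse events that has no counterpart among the primary outcomes and that RIC is not expected to produce for the events spelled out

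*Protocol article*

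**What the plan says.** All references are to the protocol article.

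- **Abstract, Results.** The primary goal is feasibility, assessed "by measuring serious RIC-related adverse events and any reduced incidence of adverse events during the trial", together with potential efficacy on the four scales. The next sentence makes safety the secondary goal.
- **Outcomes for feasibility and efficacy.** Here the primary endpoints rest on the scales alone: "The primary outcomes of this study are to assess the feasibility and efficacy of RIC from changes of ESS, PSQI, PDSS-2, and PDQ39 scores". The section also asks whether the scales can be performed in these patients. It contains no adverse event measure.
- **Outcomes for safety.** Safety is the secondary outcome. The serious RIC-related events listed are "inability to tolerate RIC or sham-RIC procedures leading to the suspension of the study" and "signs of tissue or neurovascular injury caused by RIC and sham RIC operations". The section adds: "All adverse events will be independently determined by trained individuals of the research group who are blinded by random grouping".
- **Abstract, Methods.** The same two kinds of event appear as examples: "adverse events, such as inability to tolerate the treatment leading to suspension of the study".
- **Interventions.** The RIC arm receives "five cycles of cuff inflation to 200 mmHg for 5 min, followed by deflation for 5 min". For the comparator, "Patients in the sham-RIC group receive the same procedure except the maximum inflation pressure is 60 mmHg".
- **Statistical analysis.** The data come from patients who complete the protocol and follow-up, analysed per protocol. Categorical variables are compared by chi-square at P < 0.05.

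**The concern.** A measure of a primary goal needs a stated event, comparator and period, and a good result should satisfy it. The reduction phrase lacks all three elements, and its expected direction is doubtful. The two kinds of event that the article spells out arise from the procedure itself, so there is no pre-treatment incidence to lower. Against sham, the RIC arm has the same procedure at a higher pressure, and the article gives no mechanism by which that would mean fewer intolerant or injured patients.

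What is at stake is the reading of the result. A trial in which nobody is harmed in either arm shows no reduction, although that is the best feasibility result available. A trial in which sham happens to have one or two more affected patients shows a reduction that could be reported as meeting part of the primary goal. The reader also cannot tell whether adverse events are primary or secondary.

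**Working it through.** **1. The role of adverse events, section by section**

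| Section | Role of adverse events |
|---|---|
| Abstract, Results (primary goal) | Measure of feasibility, including a reduced incidence |
| Abstract, Results (next sentence) | Safety is the secondary goal |
| Outcomes for feasibility and efficacy | None; the four scales only |
| Outcomes for safety | Secondary outcome |

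The reduction measure occurs only in the abstract. No section says what the incidence would be reduced against, for which events, or over which visits.

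**2. Inputs for the arithmetic**

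- n = 20 per arm (Sample size estimation). This follows pilot-study guidance, not a power formula, so there is no planned power to reproduce; 20 + 20 = 40 agrees with Study design.
- Event rates: none are given. The rates below are assumptions, for the proportion of patients with at least one event.
- Test: chi-square, P < 0.05 (Statistical analysis). The article does not link this test to the reduction phrase, so step 4 is illustrative.

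**3. Chance of a numerical reduction when RIC and sham have the same true rate**

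Let X (RIC) and Y (sham) be independent Binomial(20, p). By symmetry,

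P(X < Y) = [1 − P(X = Y)] / 2, where P(X = Y) = Σ P(X = k)².

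- p = 5%: P(X = 0, 1, 2, 3) = 0.3585, 0.3774, 0.1887, 0.0596. The squares are 0.1285 + 0.1424 + 0.0356 + 0.0035; with the small remaining terms the sum is 0.310. P(X < Y) = (1 − 0.310)/2 = **0.34**.
- p = 10%: the sum of squares is 0.214. P(X < Y) = (1 − 0.214)/2 = **0.39**.

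So with no true difference, RIC looks numerically better in roughly a third or more of trials at these rates.

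**4. What a significant reduction would need**

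With 0/20 on RIC and s/20 on sham, Pearson's statistic is 40·(20s)² / [20·20·s·(40 − s)] = 40s/(40 − s).

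- s = 3: 120/37 = 3.24, P = 0.072.
- s = 4: 160/36 = 4.44, P = 0.035.

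The threshold depends on the version of the test: 4/20 by uncorrected chi-square, 5/20 by Fisher (P = 0.047), 6/20 by Yates (P = 0.027). The probability of a significant reduction by uncorrected chi-square, summed over all binomial outcomes, is 0.6% if both rates are 5%, 1.9% if both are 10%, and 0.02% if RIC is 20% and sham 5%.

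**5. Can a perfectly tolerated RIC show a reduction at all?**

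Yes, if sham has at least one affected patient. With 0/20 on RIC the chance is 1 − (1 − p)²⁰ for sham rate p: 0 at 0%, 18% at 1%, 64% at 5% and 88% at 10%. It is impossible only when sham has no events.

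**6. Analysis set**

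The first listed event is intolerance that leads to stopping. If the completers-only set is applied to adverse events, such patients drop out of the numerator and the denominator, so the count would miss the event it is meant to record.

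**The case against.** The best reply is that the phrase is loose abstract wording and that nothing operative depends on it. Several parts of that reply stand, and they rule out stronger readings that a reader might reach.

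- **That RIC can never show a reduction.** Not supported. Sham patients also wear an inflated cuff and their events are counted, so 0/20 against one or more is a reduction (step 5).
- **That every adverse event in the plan is cuff harm.** Not supported. The abstract's Methods give the events as examples, the safety section labels its list as serious RIC-related events, and it then refers to all adverse events. Other events are neither listed nor excluded, and a condensed article may leave them to the full protocol.
- **That the plan tests in the wrong direction and would hide harm.** Not supported. No directional hypothesis is stated, the chi-square test is non-directional, and serious RIC-related events are measured in the same sentence.
- **That 0/20 against 0/20 would be scored a failure.** No scoring rule exists. The result simply shows no reduction.

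It can also be said that a fall in incidence between the visits at days 7, 14, 28 and 90 may have been meant. That is possible, but it confirms that the comparator and period are undefined. None of these points gives the phrase a meaning or a place among the primary outcomes.

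**Conclusion.** The concern holds as an undefined and inconsistently placed measure that is unsuitable for feasibility. The contradiction in roles is plain from the text and needs no assumption. The unsuitability rests on the events that the article spells out and on its giving no reason to expect fewer of them at 200 mmHg than at 60 mmHg.

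The practical size is a 34% to 39% chance that a purely random numerical reduction could be credited to the primary goal, at equal assumed rates of 5% to 10%. A statistically significant one is rare at those rates (0.6% to 1.9%), so the risk lies in the open wording, which accepts a reduction of any size. These figures depend on the assumed rates and on independent patients with 20 analysed per arm. Detection of excess harm is not blocked by the phrase. It could be weakened if adverse events are counted only in per-protocol completers.

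**What to change.** 1. Delete the reduced-incidence phrase from the primary goal in the abstract's Results.
2. Give adverse events one role throughout the abstract's Results, Outcomes for feasibility and efficacy, and Outcomes for safety.
3. Report, by arm and in all randomised patients, the number and percentage with any adverse event and, separately, with a cuff-related event. Give the RIC-minus-sham difference with a 95% CI.
4. State that the per-protocol completer set does not apply to adverse events, and that no reduction is claimed.

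The cost is wording and a little more analysis. If the full protocol already collects all adverse events, items 3 and 4 only fix how they are tabulated. No visit, procedure or sample size changes.

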**Conclusion:**

This study is a prospective randomized controlled trial to determine the safety, feasibility, and potential efficacy of RIC for patients with Parkinson's disease associated with EDS.

## Introduction

Parkinson's disease is the second most common neurodegenerative disease following Alzheimer's disease, affecting more than 10 million people worldwide (1, 2). Because it has a progressive and chronic course, improving the quality of patients' life is vital. Sleep disturbances are common non-motor symptoms of Parkinson's patients, affecting ~90% of this population (3), and can significantly affect the quality of life (4–8).

Excessive daytime sleepiness (EDS) is a common sleep disorder of Parkinson's disease with an incidence rate as high as 16–50%. EDS limits patients' ability to independently execute activities of daily living (9). The mechanisms of EDS in Parkinson's disease are complex and involve different areas of neuronal degeneration of the brain. Decreased dopamine levels, blunting of circadian melatonin release, and degeneration of human photosensitive retinal ganglion cells are potential causes of sleep and circadian rhythm disorder of Parkinson's disease (3, 10, 11). Human melanopsin-containing retinal ganglion cells (mRGCs) are retinal photoreceptors regulating pupillary light reflection and diurnal light concentration. They are found in the suprachiasmatic nucleus, responsible for regulating circadian rhythm as well as mood and sleep behaviors. MRGCs are found to be damaged in Parkinson's disease and this is thought to be one of the main mechanisms of circadian rhythm disorders in Parkinson's disease (12). In other words, protecting mRGC can be beneficial for maintaining circadian rhythm and ultimately improving the quality of life of patients with Parkinson's disease (11).

Although there are treatment options considered for EDS, they are not without challenges. Examples include modafinil, methylphenidate, caffeine, istradefylline, and atomoxetine. Unfortunately, these drugs have not been carefully evaluated for EDS associated with Parkinson's disease and carry adverse effects (8, 13–16).

Remote ischemic conditioning (RIC) refers to a therapy in which a short-term sublethal blood flow block is administered to a distal limb, which induces endogenous protection with several vasoactive and neurogenic biochemicals, protecting the vital organs from destructive ischemic injury (17). Numerous studies have shown that RIC can induce anti-apoptosis, anti-inflammation, anti-oxidation, and mitochondrial regulation, and improve neural function (18–24). RIC maximizes motor and cognitive function and reduces the size of penumbral infarcts after ischemic stroke to similar extents to physical exercise therapy (25, 26). RIC also has a benign effect on sleep (27). In an animal study, RIC selectively increases the daily sleep volume of non-rapid eye movement (NREM), or the sleep state for tissue recovery, repair, and removal of metabolic wastes, and plays an important role in neuroprotection of ischemic adaptation (27). Kim has found that RIC reduces the loss of functional dopaminergic cells in the substantia nigra pars compacta (SNC) and indicates its potential therapeutic role (28). In addition, RIC has been reported to promote the survival of retinal ganglion cells for the regulation of sleep-wake cycles after various optic nerve injuries (29–32). Gidday further notes that RIC protects the retina from acute and chronic injury, supporting its role as a therapy for sleep-wake cycles (33).

This study hypothesizes that RIC reduces the loss of dopaminergic cells in the brain and improves the survival of retinal ganglion cells–including mRGCs–in Parkinson's disease, resulting in improvement of circadian rhythm disorders and reduction of EDS and sleep dysfunctions. This study conducts a single-center, double-blind, randomized controlled trial to evaluate the safety and feasibility of RIC as a non-pharmacologic therapy to reduce EDS and improve the quality of life of patients with Parkinson's disease. The findings of this study can bring more hope to the community of patients with Parkinson's disease.

## Subjects and methods

### Study design

All participants will be informed of the clinical research and the requirements for giving informed consent. The research plan and informed consent form are to be approved by the regional ethics committee; the trial has been registered at www.chictr.org.cn (Registration number: ChiCTR2200058430).

Forty patients are to be randomly assigned to the intervention (“RIC”) or control group (“sham RIC group”) with 20 patients in each group. Within the 24 h of grouping, each group starts RIC or sham RIC treatment for 45 min once a day for 28 days.

### Patient population

Participants will be recruited from outpatient and inpatient centers. The enrollment criteria are as follows: (1) diagnosis of Parkinson's disease according to MDS clinical criteria; (2) age of 18–90 year olds; (3) ESS score ≥10; (4) written informed consent obtained from the participants or legally authorized representative. Exclusion criteria are the following: (1) contraindication of ischemic conditioning (e.g., severe soft tissue injury, fracture, and peripheral vascular disease of bilateral upper extremities); (2) hemodynamic instability (i.e., systolic blood pressure > 180 mmHg, diastolic blood pressure > 110 mmHg, heart rate < 40 beats/min or > 100 beats/min, percutaneous oxygen saturation ≤ 92%, or body temperature ≥ 38.5°C); (3) life expectancy ≤ 1 year; (4) unstable comorbidities associated with the lungs, liver, and kidney (e.g., severe abnormal pulmonary function, hepatic insufficiency, renal insufficiency); (5) coagulopathy or active bleeding; (6) complications associated with acute coronary syndrome or severe arrhythmia; (7) pregnancy or nursing; (8) participation in another ongoing clinical trial.

Epworth Sleepiness Scale (ESS) is widely utilized in clinical settings to evaluate the severity of EDS. A score of 10 is typically used as a cutoff to indicate sleepiness with higher scores for more sleepiness (34). In this study, those with ESS ≥ 10 are recruited.

### Randomization

All registered patients will be randomly assigned to the intervention group or the control group with a ratio of 1:1. Randomizing the sequence column order will be performed according to the predefined table generated by a computer software program. The random sequence will be hidden in a closed opaque envelope. Before initiating the study, the envelopes will be prepared by research assistants who are not directly involved in the research project. After recording baseline measures, participants will be randomly allocated to either the RIC or control group by the treating physicians who will open the sealed opaque envelopes.

### Interventions

Within 24 h of enrollment, an RIC operation is to be performed *via* bilateral limb ischemic preconditioning (Doctormate, IPC-906D, produced by Beijing Renqiao Institute of Neuroscience). Electronic tourniquet cuffs are placed on both arms. Participants in the intervention group undergo five cycles of cuff inflation to 200 mmHg for 5 min, followed by deflation for 5 min (Figure 1). In other studies, physical treatments, such as bright light therapy (35) and multidisciplinary intensive rehabilitation (36), have been applied to patients for 28 days to alleviate sleep disorders of Parkinson's disease. Additionally, RIC has been used for patients from 7 to 300 days (37–43). As the first step to determine safety, the duration of RIC in this study is decided to be 28 days. Patients in the sham-RIC group receive the same procedure except the maximum inflation pressure is 60 mmHg (40) (Figure 2).

**Figure 1 F1:**
[figure not shown]
Remote ischemic conditioning (RIC) with an electronic tourniquet cuff device.

**Figure 2 F2:**
[figure not shown]
Procedure timeline **(A)** RIC group; **(B)** Control group (Sham-RIC).

Epworth Sleepiness Scale, the Pittsburgh Sleep Quality Index (PSQI), and Parkinson's Disease Sleep Scale-2 (PDSS-2) are to be used to assess the common sleep problems of Parkinson's patients (44, 45). The Parkinson's Disease Questionnaire 39 (PDQ39) is to be used to assess the quality of life of Parkinson's patients (46), which is administered by trained investigators blinded to the treatment assignment. The assessments are performed on the day of enrollment for baselines and 7, 14, 28, and 90 days after the enrollment.

Patients will continue their home medications to manage chronic conditions, including Parkinson's disease, according to the recommendations of the International Parkinson and Movement Disorder Society (15, 47).

### Outcomes

#### Outcomes for feasibility and efficacy

The primary outcomes of this study are to assess the feasibility and efficacy of RIC from changes of ESS, PSQI, PDSS-2, and PDQ39 scores from the baselines to post-treatment on days 7, 14, 28, or 90. This study will determine (1) whether ESS, PSQI, PDSS-2, and PDQ39 can be performed in the patients and (2) the differences between ESS, PSQI, PDSS-2, and PDQ39 in patients with or without RIC. Certified therapists and assistants will collect data from the subjects and the obtained information will be used for statistical analysis.

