### Sample size estimation

This is a phase 1 test measuring the safety and feasibility of RIC. Because there has not been a clinical study on RIC for Parkinson's patients, there is no data for reference at this point. Hertzog (48) suggests that 10–20 patients in each group are enough to evaluate the feasibility of a pilot study. Dobkin et al. explain that most phase 1 clinical rehabilitation pilot studies start with samples of 6–12 participants (49). Based on studies addressing the safety and feasibility of RIC, this project targets 20 patients in each group. The results of this study will be used not only to determine the safety and feasibility of RIC but also to estimate the sample size and calculate the power required for the phase 2 test in the future.

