Excessive daytime sleepiness is a common non-motor symptom of Parkinson's disease and manifests as an inability to remain awake during the daytime, fatigue, and sudden collapse. Due to severe dyskinesia in the middle and late stages, patients with Parkinson's disease rely on others for their daily activities. Non-pharmacologic treatment options are currently limited and available therapies, including sports rehabilitation therapy, cognitive behavioral therapy, light treatment, repetitive transcranial magnetic stimulation, and deep brain stimulation (18), are not universally suitable for patients with Parkinson's disease in different stages of their illness. In contrast, RIC is inexpensive and easy to administer especially for patients with risk of falls, limb movement disorder, and inability to participate in traditional rehabilitative activities.

This project will administer RIC to patients with Parkinson's disease in different stages to determine its safety and feasibility. Effectiveness in reducing EDS will be analyzed as well. The results could provide an opportunity to develop a non-pharmacological treatment that is easy and simple to administer for EDS and benefits the community of patients with Parkinson's disease.

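### Efficacy is ranked primary and safety secondary, yet the trial is described and sized as a phase 1 safety and feasibility test, and no exploratory label keeps a scale P value from being read as a primary verdict

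*Protocol article*

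**What the plan says.** The protocol article assigns the roles of efficacy, feasibility and safety in several places.

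- **Outcomes for feasibility and efficacy:** this subsection opens with "The primary outcomes of this study are to assess the feasibility and efficacy of RIC". Both are to be read from changes on the four scales, taken "from the baselines to post-treatment on days 7, 14, 28, or 90". The second of its two questions is a between-group comparison: "the differences between ESS, PSQI, PDSS-2, and PDQ39 in patients with or without RIC".
- **Outcomes for safety:** "The secondary outcome of this study is to assess the safety of RIC". The serious RIC-related adverse events are defined here.
- **Abstract, Results:** feasibility and potential efficacy form the primary goal, and safety the secondary one. Feasibility is to be measured by serious RIC-related adverse events.
- **Introduction, last paragraph:** the trial is "to evaluate the safety and feasibility of RIC as a non-pharmacologic therapy to reduce EDS".
- **Sample size estimation:** "This is a phase 1 test measuring the safety and feasibility of RIC". The section cites a 10–20 per group rule for pilot feasibility and 6–12 participants for phase 1 rehabilitation pilots, says no reference data exist, settles on 20 per group, and expects the results to supply the sample size and power for phase 2.
- **Discussion, last paragraph:** safety and feasibility come first, and then "Effectiveness in reducing EDS will be analyzed as well".
- **Statistical analysis:** P<0.05 is the significance threshold for comparisons in general, and the analysis is per-protocol.

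**The concern.** The label primary tells readers which result the trial is to be judged on. If the Outcomes section governs, the group differences on the Epworth Sleepiness Scale (ESS), Pittsburgh Sleep Quality Index (PSQI), Parkinson's Disease Sleep Scale-2 (PDSS-2) and Parkinson's Disease Questionnaire 39 (PDQ39) carry that weight. If the sample-size section governs, the same differences are planning input for phase 2, and the trial is judged on safety and feasibility.

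Nothing in the article sizes an efficacy comparison, and nothing says that the scale comparisons are exploratory. The P<0.05 threshold covers them by default. A non-significant scale could then be reported as RIC not working, and a significant one as RIC working, when neither question was planned for. The adverse events have a similar problem: the same events serve the primary goal in the Abstract and the secondary outcome in the Outcomes section.

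**Working it through.** **1. The sections side by side**

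| Section | Efficacy | Feasibility | Safety |
|---|---|---|---|
| Abstract, Results | within primary goal (potential efficacy) | primary, by serious adverse events | secondary |
| Outcomes | primary | primary, by whether the scales can be performed and by score changes | secondary, by the same adverse events |
| Introduction, aim | purpose of the therapy, not ranked | named as aim | named as aim |
| Sample size estimation | not named | named as purpose | named as purpose |
| Discussion, end | additional | named as purpose | named as purpose |

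The Abstract and Outcomes agree on rank. They differ from the sample-size section on whether efficacy is a main question and on where safety stands. Feasibility is common to all five, so it is not in dispute as a primary aim. How it is measured is in dispute.

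**2. The plan's own figure**

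The 20 per group cannot be reproduced by a formula, because no effect size, SD, power or precision target is given. It is the top of the cited 10–20 range.

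**3. What 20 per group gives for one efficacy comparison**

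Inputs: n = 20 per group and 1:1 allocation (Sample size estimation, Randomization); alpha 0.05 (Statistical analysis), taken as two-sided by assumption; independent-samples t-test (Statistical analysis). The standardised difference d is assumed over a range.

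Power is taken from the noncentral t distribution with 2n − 2 degrees of freedom and noncentrality d × √(n/2). With n = 20 there are 38 degrees of freedom, and √(20/2) = 3.162.

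| Assumed d | Noncentrality | Power, 20 per group | n per group for 80% power |
|---|---|---|---|
| 0.3 | 0.95 | 15% | 176 |
| 0.5 | 1.58 | 34% | 64 |
| 0.8 | 2.53 | 69% | 26 |

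The d that gives 80% power is 0.91. The 95% confidence interval half-width for a difference is t(0.975, 38) × √(2/20) = 2.024 × 0.316 = 0.64 SD.

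Per-protocol analysis can only lower n. With an assumed 20% non-completion, 16 per group remain. Power at d = 0.5 falls to 28%, 80% power needs d = 1.02, and the half-width is 2.042 × √(2/16) = 0.72 SD.

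**4. Why step 3 cannot be read as the trial's chance of success**

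The Outcomes section names four scales and four visits and singles out none, so there are 4 × 4 = 16 comparisons. I simulated 20 per group, testing each comparison at 0.05, with an assumed common correlation between comparisons of 0.5 or 0.8:

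| True d on every comparison | At least one P<0.05, correlation 0.5 | Correlation 0.8 |
|---|---|---|
| 0.5 | about 86% | about 66% |
| 0 | about 38% | about 21% |

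A single comparison usually misses a moderate effect, while some comparison among the sixteen often reaches significance, even with no effect. The risk of misreading therefore runs both ways.

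**5. Precision for safety**

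With no events among 20 RIC patients, the one-sided 95% upper limit is 1 − 0.05^(1/20) = 13.9%. Calling safety primary would not make it precisely estimated.

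**The case against.** The case for leaving the text alone has several parts.

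- *The stated ranking is consistent.* The Abstract and both Outcomes subsections give the same order, and no section says that safety is primary. This stands. The conflict is between that ranking and the description and sizing in the sample-size section, with the Introduction and Discussion as support.
- *The sizing matches a primary outcome.* The only per-group rule cited concerns feasibility, which is already primary. A reader might infer that the trial was sized for safety and that safety was then demoted. The article does not support this: safety is part of the stated purpose, but no event rate or precision for it is given. What remains is that efficacy is primary without any sizing.
- *No verdict rule is written.* The P<0.05 threshold is general and not tied to the primary outcome, the Abstract says potential efficacy, and the sample-size section already foresees use for phase 2. A reader might infer a planned headline verdict on efficacy. The text does not go that far. It leaves such a reading open, because the threshold covers the scales and they carry no exploratory label.
- *A pilot need not be powered.* Agreed. The point asks for no more patients.
- *The power figures suggest failure.* A reader might infer that a true moderate effect would be recorded as a failed primary outcome about two times in three. That holds only for one scale at one visit, which is not the plan as written.

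**Conclusion.** The point holds as an inconsistency in the outcome hierarchy that affects what the trial may conclude. Efficacy is primary (potential efficacy in the Abstract) and safety secondary in the Abstract and Outcomes, while the sample-size section describes and sizes a safety and feasibility test. The adverse events serve two outcomes of different rank. No statement prevents a P value on an unsized efficacy comparison from being taken as the primary answer.

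Its size can be stated for a single comparison only: 34% power at an assumed 0.5 SD, and 0.91 SD needed for 80%. Effect sizes, two-sided testing, non-completion and correlations are assumptions, since the article gives none of them. The contradiction between sections needs no assumption. The documents do not make promotion of safety to primary the only correct repair; that depends on which purpose the sponsor keeps.

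**What to change.** 1. State one hierarchy across the Abstract, both Outcomes subsections and Sample size estimation. Feasibility is primary; safety joins it if the sponsor keeps the purpose given in the sample-size section.
2. Assign the serious RIC-related adverse events to one outcome only, and define feasibility the same way in the Abstract and the Outcomes section.
3. Label the ESS, PSQI, PDSS-2 and PDQ39 group differences exploratory, and report them as estimates with 95% confidence intervals for phase 2 planning.
4. Add to Statistical analysis that P<0.05, or its absence, on a scale will not be used to conclude that RIC is or is not effective.

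**Cost:** changes of wording, with no extra patients, visits or data. The trial gives up a confirmatory efficacy claim. It is registered and ethics-approved, so both records need updating if the outcome labels change.
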